### Study procedures

At each study visit, participants will undergo a set of clinical assessments which will comprise measurement of height, weight, waist circumference, office BP, oxygen saturations and heart rate. Body mass index (BMI) will be calculated from weight and height. An ECG will be performed. A manual of procedures has been collated for the study procedures below and kept in the study site file.

### Clinic BP

Clinic BP will be measured as per the British and Irish Hypertension Society (BIHS) guidelines using a validated BP monitor and an appropriate cuff based on the brachial arm circumference.^7^ The patient will be seated for at least 5 min, relaxed and not moving or speaking. BP will be measured in both arms, and the arm with the highest BP is selected. The measurement will be repeated a further two times, at least 1 min apart and the mean of readings two and three will be used. The appropriate cuff size will be used depending on the brachial arm circumference.

### Ambulatory BP monitoring

ABPM using Spacelabs 90217RM over 24 hours will be measured at each study visit according to BIHS guidelines.^7^ Participants will undergo ABPM for 24 hours with daytime readings every 30 min (0700–2159) and night-time readings every 60 min (2200–0659). The ABPM report is considered valid if there are 14 daytime measurements obtained. An appropriate cuff size will be used depending on the brachial arm circumference.

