### Study objectives and statistical analysis

#### Primary outcome

The primary outcome is the average 24-hour ABPM SBP (all day and night) at 12 months in SARS-CoV-2 positive cases and in SARS-CoV-2 negative controls

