#### Secondary outcomes

Secondary outcomes are the average of the following measures SARS-CoV-2 positive cases and in SARS-CoV-2 negative controls at 12 months and 18 months: 24-hour ABPM diastolic BP (DBP); day ABPM SBP; day ABPM DBP; night ABPM SBP; night ABPM DBP; 24-hour ABPM HR and 24-hour urine sodium

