### Sample size calculation

From the OBELIX pilot study, we have established that ABPM SBP is normally distributed with a SD of 10 mm Hg. A mean difference of 5 mm Hg ABPM SBP between groups was determined to be the minimum clinically relevant difference. We will require 64 COVID-19 cases and 64 non-COVID control subjects to reject the null hypothesis with an alpha=0.05% and 80% power. The study requires a total of 150 subjects to be recruited (128 completed subjects) after accounting for approximately 15% missing data and ABPM errors (typical for ABPM studies). OBELIX has recruited 48 subjects and these participants will be invited into LOCHINVAR. The LOCHINVAR study will recruit the remaining subjects.

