### Statistical analysis

The primary analysis (primary outcome 24-hour ABPM SBP at 12 months) will use linear regression to compare 24-hour ABPM SBP between SARS-CoV-2 positive and SARS-CoV-2 negative subjects with adjustment for covariates including age, sex and BMI. The adjusted mean difference, with a 95% CI and associated p value, will be reported.

Secondary analyses will extend this regression model to examine the impact of baseline patient characteristics, and to investigate the possibility of interactions with COVID-19 clinical status. For longitudinal analysis we shall use linear mixed models as appropriate to compare changes in the mean 24-hour ABPM SBP between SARS-CoV-2 positive and SARS-CoV-2 negative subjects with adjustment for baseline 24-hour ABPM SBP and baseline covariates.

All statistical analyses will be performed using R Software V.4.0.2 or later.

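### The ABPM validity rule counts daytime readings only, so a recording with no night readings can enter the primary analysis as a 24-hour value

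*Protocol article*

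**What the plan says.** Under Ambulatory BP monitoring, the protocol article schedules a reading every 30 minutes from 0700 to 2159 and every 60 minutes from 2200 to 0659. It then gives one validity condition: "The ABPM report is considered valid if there are 14 daytime measurements obtained". No condition is set on the night readings, there or elsewhere in the article.

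Under Primary outcome, the endpoint is the "average 24-hour ABPM SBP (all day and night) at 12 months". The primary analysis under Statistical analysis "will use linear regression to compare 24-hour ABPM SBP between SARS-CoV-2 positive and SARS-CoV-2 negative subjects". Secondary outcomes include "night ABPM SBP; night ABPM DBP".

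Sample size calculation takes an SD of 10 mm Hg and a smallest relevant difference of 5 mm Hg. It arrives at 64 completed participants per group, and recruits 150 to allow for about 15% missing data and ABPM errors.

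The article also says that ABPM follows the BIHS guidelines, and that a manual of procedures is kept in the site file. Neither is shown, and the article quotes no night criterion from either.

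**The concern.** The rule decides whether the ABPM report is usable, and the report is the source of the 24-hour value. Followed as written, it accepts a recording in which every night reading failed or the cuff was taken off at bedtime. The value that enters the regression is then a daytime mean labelled as a 24-hour mean. Because pressure is usually lower at night, that value is too high. The night secondary outcomes are exposed in another way: a night mean could rest on a single reading and still come from a valid report.

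Three things are at stake:

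- If night readings are lost more often in one group, the primary contrast is biased.
- If they are lost equally often in both, the extra spread costs some power in a study sized at 80%.
- In the longitudinal mixed model, losing the night at one visit only would look like a change within that participant.

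Without a stated night rule, the handling of partial recordings could also be settled after the data are seen.

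**Working it through.** **The plan's own figure.** Inputs from Sample size calculation: difference 5, SD 10, power 80%. The normal approximation at two-sided alpha 0.05 gives n = 2 × (1.96 + 0.84)² × 10² / 5² = 62.8, so 63 per group. The two-sample t-test gives 63.8, so 64 per group, with power 0.801 at 64. The stated 64 is reproduced. (Alpha is printed as 0.05%; 64 follows only from 0.05, which is used here.) For recruitment, 128 / 0.85 = 150.6, against 150 stated, which agrees with approximately 15%.

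**Readings scheduled.**

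- Day: 15 h at 2 per hour = 30. Night: 9 h at 1 per hour = 9.
- Required by the rule: 14 / 30 = 47% of day readings and 0 / 9 of night readings.
- Weight of night in a complete recording: 9 / 39 = 0.231 in a plain mean of all readings, or 9 / 24 = 0.375 in a mean weighted by hours. The article does not say which is used, so both are carried forward.

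**Shift in one recording with no night readings.** The day mean then stands in for the 24-hour value. Shift = night weight × (day mean − night mean). The day-night difference is not in the documents; 10 to 20 mm Hg is assumed.

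| Assumed day-night difference (mm Hg) | Against plain mean (× 0.231) | Against time-weighted mean (× 0.375) |
|---|---|---|
| 10 | 2.3 | 3.75 |
| 15 | 3.5 | 5.6 |
| 20 | 4.6 | 7.5 |

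**Bias in the group contrast.** Bias = (difference between groups in the share of recordings without night readings) × shift. The shares are illustrative; the documents give none.

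- 10 percentage points: 0.10 × 2.3 = 0.23, up to 0.10 × 7.5 = 0.75 mm Hg.
- 30 percentage points: 0.30 × 2.3 = 0.69, up to 0.30 × 7.5 = 2.25 mm Hg.

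**Noise with no imbalance.** If a share f of recordings in both groups lacks night readings, independently of the participant's true level, SD = √(10² + f(1 − f) × shift²). In the time-weighted case:

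- f = 0.10, shift 3.75: √(100 + 0.09 × 14.06) = 10.06; power at 64 per group 0.797.
- f = 0.30, shift 7.5: √(100 + 0.21 × 56.25) = 10.57; power 0.756.

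Power therefore runs from about 0.80 to 0.76. The plain-mean shifts are smaller and cost less.

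**The case against.** The strongest reply is that the gap may be closed elsewhere. A manual of procedures covers ABPM, the BIHS guidelines are cited, and an analysis plan may exist. Any of these could hold a night criterion, so it cannot be said that the study lacks one. That limits the claim to the article, but it does not remove it. The article does not leave validity to another document: it states a rule, and the rule does not cover the night part of the primary outcome. If a night criterion exists, the two texts need to be brought together.

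Two stronger readings are tempting, and the documents support neither.

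- A reader might infer that the error is as large as the whole 5 mm Hg target, because 5.6 mm Hg appears in the table above. That figure is a shift in one person's recording; the target is a difference between group means. Even at the largest shift, an imbalance of 5 / 7.5 = 67 percentage points would be needed to create a 5 mm Hg bias. At any shift below 5 mm Hg, imbalance alone could not do it.
- A reader might infer that night is under-weighted in the primary outcome, at 23.1% instead of 37.5%. That holds only for a plain mean of readings, which the article does not specify; an averaging formula is commonly left to the analysis plan. Even under a plain mean, the offset in complete recordings, 20 × (0.375 − 0.231) = 2.9 mm Hg at most, applies to both groups and cancels from the contrast if they dip equally.

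It is also fair to say that more frequent loss of night readings in cases is conjecture. The documents give neither the frequency nor the imbalance.

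**Conclusion.** The point holds in a limited form. As published, the validity rule does not match the primary outcome or the night secondary outcomes, and it admits a daytime mean as a 24-hour value. This follows from the text and needs no assumption.

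The size does rest on assumptions: a day-night difference of 10 to 20 mm Hg, an unstated averaging method, and illustrative shares of recordings without night readings. Within those ranges the likely effect on the contrast is well below the 5 mm Hg target: about 0.2 to 0.75 mm Hg at a 10-point imbalance and 0.7 to 2.25 mm Hg at 30 points. With no imbalance there is no mean bias from this source, and power falls to 0.76 only in the most extreme case examined. The direction depends on which group loses more nights: more loss among cases would overstate a COVID-19 effect, and more among controls would understate it.

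This should be corrected because it concerns the definition of the primary endpoint and is cheap to settle in advance. It does not show that the planned comparison is invalid.

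**What to change.** Extend the rule under Ambulatory BP monitoring. Keep the daytime condition, and add that the 24-hour and night values also require a minimum number of night readings. The investigators should choose that number before the data are examined and make it consistent with the manual of procedures; the documents give no basis for naming one here. State that the 24-hour and night values are treated as missing when the minimum is not met, while the day values can stand on the daytime rule.

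As an optional safeguard, the 24-hour value could be computed as (15 × day mean + 9 × night mean) / 24, so that uneven loss of readings does not change the weight of night from one participant to the next. The article states no other formula, so this is not the correction of an error.

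The change is to wording only. The cost is that some recordings become invalid for the primary outcome. They draw on the allowance of 150 − 128 = 22 participants, which also has to cover all other missing data and ABPM errors. The number lost for lack of night readings should therefore be tracked by group during the study.

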### Brachial flow-mediated dilation

At each study visit brachial flow-mediated dilation (FMD) will be measured using the UNEX EF38G device (UNEX Corporation, Nagoya, Japan) as previously described and based on the Glasgow Clinical Research Facility Standard Operating Procedures.^8^ In brief, the participant lies supine with their arm outstretched. A BP cuff is fitted on the forearm and the ultrasound probe is placed 5–10 cm proximal to the elbow using the probe holder. The brachial artery is identified in the short axis using the ultrasound probe. The automated tracking system activated to adjust the probe position. A baseline reading is obtained for 3 min. The occlusion cuff is then inflated 50 mm Hg above SBP for 5 min. At the end of this 5 min period, the maximum diameter is measured automatically, and the cuff is deflated and the brachial artery is tracked for 2 min. Automated outputs for rest diameter, maximum diameter and %FMD will be recorded. Additional manual quality checks and analysis were performed by a single operator (SL) where required. The %FMD is calculated as [(Max Diameter-Rest Diameter)/Rest Diameter]×100

### 6 mi walk test

The participant will sit for 10 min after which they will be asked to walk as long as possible between two markers for a maximum of 6 min to assess their exercise tolerance supervised by the research team. Level of shortness of breath and fatigue using the Borg scale, BP, oxygen saturations and heart rate will be measured pre and post 6 min walk test. This procedure has been modified from the American Thoracic Society and the Australian Lung Foundation/Australian Physiotherapy Association guidelines.^9 10^

### Questionnaires (Patient Health Questionnaire-9 and Euroqol 5-Dimension 3-Level)

The participant will be asked to complete the Patient Health Questionaire-9^11^ and Euroqol 5-Dimension 3-Level.^12^

### Blood samples

Blood sampling through venepuncture will be performed with samples collected in appropriate containers as described in table 1. Routine clinical biochemistry and haematology samples are sent to the local NHS laboratory. Samples taken for RAS fingerprinting (Attoquant Diagnostics, Vienna, Austria) and future biomarkers are centrifuged and serum is separated into 1 mL aliquots (nine aliquots in total) and then stored in a −80°C freezer. Immunotyping samples will be sent on ice to the BHF Glasgow Cardiovascular Research Centre for subsequent cytokine assessments as well as cellular immunity flow cytometry assays. All samples will be stored in a linked anonymised form.

**Table 1 T1:** Blood samples

Routine clinical laboratory sampling	Full blood count, urea and electrolytes, bone profile, liver function tests, glucose, HBA1c, lipid profile, ferritin, B_12_, folate, coagulation screen, CRP
Additional clinical laboratory sampling	NTpro-BNP, D Dimer, hsTnI, renin, aldosterone, RAS fingerprinting
Urine sampling	24-hour urine collection for electrolytes (optional)
Vascular phenotyping	24-hour ABPM, ECG, brachial flow-mediated dilation (FMD), HBPM
SARS-CoV-2 antibody test	IgG antibody testing
Vascular and immune biomarkers (may be stored)	Vascular biomarkers Microparticles, oxidative stress markers (TBARS, 8-OHDG, nitrotyrosine), total antioxidant status, inflammatory biomarkers/adhesion molecules (ILs, MCP1, TNF, IFNs, sVCAM-1, sICAM, s-Selectin), RAS fingerprint ACE2 (s-ACE2, ACE2 activity), Ang peptides Immune biomarkers Trucount panel (CD3, CD4, CD8, CD14, CD19, CD45, CD56, HLA-DR), T cells (CD3, CD4, CD8, CD16, CD27, CD45RA, CD56, CD62L, TcRα/β TcRγ/δ), T cells II (CD3, CD4, CD8, CD31, CXCR4, CD27, CD45RA, CD56, CD40L), T cells III (CD3, CD4, CD45RA, CXCR5, CXCR, CCR6, CCR7, ICOS, PD-1), regulatory T cells (CD3, CD4, CD8, TcRα/β, CD25, CD45RA, CD127, FoxP3 (i/c)), B cells (CD5, CD10, CD19, CD24, CD27, CD38, CD86, IgD, IgM), Monocytes (CD4, CD14, CD16, CD19, CD45, HLA-DR), Dendritic cells (CD1c, CD16, CD11c,CD3/CD14/CD15/CD56, CD123, CD141, HLA-DR, CD80, SLAN) Future biomarker studies Blood and urine to be stored for future ethically approved biomarker studies.

ABPM, ambulatory blood pressure monitoring; CRP, C reactive protein; HBA1c, glycated hemoglobin; HBPM, home blood pressure monitoring; NTpro-BNP, N-terminal pro B-type natriuretic peptide; RAS, renin–angiotensin system.

### Urine sample and 24-hour urine collection

Participants will provide 10 mL of urine for a dipstick test and to be stored as 1 mL aliquots (three in total) in a −80°C freezer. A 24-hour cannister and an instructions sheet will be provided to participants to perform a 24-hour urine collection. The volume of 24-hour urine collected will be measured and 10 mls from the 24-hour urine sample will be aliquoted for storage while the rest will be processed in the local NHS laboratory for measurement of urine electrolytes.

### Optional study procedures

#### Home BP Monitoring

Home BP monitoring (HBPM) will be performed using OMRON M3 device in accordance with BIHS guidelines.^7^ Readings will be recorded, in triplicate, morning (0600–1200) and evening (1800–0000) for 7 days. The first day’s readings will be excluded from the mean if there are major discrepancies between the first and second reading. A minimum of five sets of morning and evening readings will be required for HBPM to be valid within a 10-day period. HBPM will be recommended for all participants if ABPM shows elevated BP.

### Adverse events

No specific adverse events are anticipated other than participant discomfort related to venepuncture, ABPM and FMD.

### Poststudy care

At each study visit, the participant will be informed results of investigations, and clinically important information will be communicated to the participant’s general practitioner.

### Study objectives and statistical analysis

#### Primary outcome

The primary outcome is the average 24-hour ABPM SBP (all day and night) at 12 months in SARS-CoV-2 positive cases and in SARS-CoV-2 negative controls

#### Secondary outcomes

Secondary outcomes are the average of the following measures SARS-CoV-2 positive cases and in SARS-CoV-2 negative controls at 12 months and 18 months: 24-hour ABPM diastolic BP (DBP); day ABPM SBP; day ABPM DBP; night ABPM SBP; night ABPM DBP; 24-hour ABPM HR and 24-hour urine sodium

#### Tertiary outcomes

Tertiary outcomes are % FMD; Exercise tolerance—distance walked in 6 min; Quality of life and mood—difference in longitudinal changes in QoL and mood between groups; mean HBPM SBP; mean HBPM DBP; day HBPM SBP; evening HBPM SBP; day HBPM DBP and evening HBPM DBP at 12 months and 18 months.

### Sample size calculation

From the OBELIX pilot study, we have established that ABPM SBP is normally distributed with a SD of 10 mm Hg. A mean difference of 5 mm Hg ABPM SBP between groups was determined to be the minimum clinically relevant difference. We will require 64 COVID-19 cases and 64 non-COVID control subjects to reject the null hypothesis with an alpha=0.05% and 80% power. The study requires a total of 150 subjects to be recruited (128 completed subjects) after accounting for approximately 15% missing data and ABPM errors (typical for ABPM studies). OBELIX has recruited 48 subjects and these participants will be invited into LOCHINVAR. The LOCHINVAR study will recruit the remaining subjects.

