**Methods and analysis:**

The LOCHINVAR study is an observational clinical phenotyping study comparing longitudinal BP change between individuals with and without COVID-19 infection. 150 participants (30–60 years) with no history of hypertension and not on BP lowering medications will be recruited to the study to attend three visits (baseline, 12 months, 18 months). Cases will be patients who were admitted to the Queen Elizabeth University Hospital (QEUH), Glasgow, UK, with suspected/confirmed COVID-19 until 31 December 2021 and who were alive at discharge. Controls will be those who have never had confirmed COVID-19 infection. All participants will undergo clinical and vascular phenotyping studies which will include 24-hour ambulatory BP monitoring systolic BP (ABPM SBP), brachial flow-mediated dilatation urine and blood samples to assess the renin-angiotensin system, vascular inflammation and immune status. The primary outcome is the change in systolic 24-hour ABPM (ABPM SBP) between the cases and controls. Sample size was calculated to detect a mean difference of 5 mm Hg ABPM SBP at 80% power.

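### The sample size paragraph prints alpha as 0.05%; 64 per group gives 80% power only at a two-sided 5% level, and about 24% at the level printed

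*Protocol article*

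**What the plan says.** The Sample size calculation section of the protocol article gives every input to the calculation:

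- **Variability:** from the pilot study, "ABPM SBP is normally distributed with a SD of 10 mm Hg".
- **Difference to detect:** "A mean difference of 5 mm Hg ABPM SBP between groups was determined to be the minimum clinically relevant difference".
- **Size, significance level and power:** "We will require 64 COVID-19 cases and 64 non-COVID control subjects to reject the null hypothesis with an alpha=0.05% and 80% power".
- **Recruitment:** 150 participants, to leave 128 completers after about 15% missing data and ABPM errors.

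The abstract repeats the difference and the power but gives no alpha: "Sample size was calculated to detect a mean difference of 5 mm Hg ABPM SBP at 80% power". The Statistical analysis section names no significance level either. For the primary comparison it says: "The adjusted mean difference, with a 95% CI and associated p value, will be reported". The 0.05% in the sample size paragraph is thus the only significance level in the article, and the article gives no reason for so strict a value.

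**The concern.** An alpha of 0.05% is 0.0005, one hundredth of the usual 0.05. The same sentence ties it to rejecting the null hypothesis, together with 64 per group and 80% power. A test at 0.0005 needs far more participants than a test at 0.05 for the same difference and SD, so it was doubtful that the printed size, power and alpha could belong to one calculation.

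The stake is the criterion for the primary comparison. Take a primary p value of 0.01. It falls short of the printed level and meets the level the sample size implies. If the discrepancy is left until results are known, any correction could look as though it was chosen to suit them.

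**Working it through.** **Inputs.** All come from the Sample size calculation section: difference δ = 5 mm Hg, SD σ = 10 mm Hg, n = 64 per group, 1:1 allocation, power 80%, alpha printed as 0.05%. The section does not say whether the test is one-sided or two-sided, so both were tried. The calculation is for an unadjusted comparison of two means, which is what these inputs describe.

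**Step 1. Reproduce the plan's figure at two-sided alpha = 0.05.**

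Normal approximation: n per group = 2(σ/δ)²(z₁₋α/₂ + z₁₋β)² = 2 × (10/5)² × (1.960 + 0.842)² = 8 × 7.85 = 62.8, so 63.

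The t-test calculation, using the noncentral t distribution, gives 63.8, so 64 per group. This is the plan's number.

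Power with 64 per group: the noncentrality is δ / (σ√(2/n)) = 5 / (10 × √(2/64)) = 2.828, with 126 degrees of freedom. The critical t is 1.979 and the power is 80.1%. The normal approximation gives Φ(2.828 − 1.960) = 80.7%.

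**Step 2. Repeat at the printed level, two-sided alpha = 0.0005.**

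The noncentrality is still 2.828, but the critical t rises to 3.574. Power falls to 23.6%. The normal approximation gives Φ(2.828 − 3.481) = 25.7%.

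n for 80% power: the normal approximation gives 8 × (3.481 + 0.842)² = 149.5, so 150 per group. The t-test gives 152.5, so 153 per group, or 306 completers against the planned 128. With 64 per group, the true difference that gives 80% power at this level is 7.8 mm Hg, not 5.

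**Step 3. Try the one-sided readings.**

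| Alpha | Sides | Power with 64 per group (t-test) | n per group for 80% power (t-test) |
|---|---|---|---|
| 0.05 | two | 80.1% | 64 |
| 0.05 | one | 87.9% | 51 |
| 0.0005 | two | 23.6% | 153 |
| 0.0005 | one | 30.1% | 140 |

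Only two-sided 0.05 returns both 64 per group and 80% power.

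**Step 4. Check the recruitment figure.** 128 / (1 − 0.15) = 150.6, so 151. The plan's 150 with approximately 15% loss agrees closely, so nothing else in the paragraph needs to move.

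**Step 5. Compare with the analysis section.** A 95% CI corresponds to a two-sided 5% test. The interval that matches a two-sided 0.05% test is a 99.95% CI, which appears nowhere.

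**The case against.** The strongest reply is that this is a typing slip that a reader can resolve from the article itself. 64 per group is exactly the t-test answer at two-sided 5%, and the analysis section plans a 95% CI. Size, recruitment target, model and interval all stay as they are. On this view the 24% power and 153 per group describe a study that nobody planned, and a reader who saw only those figures would wrongly conclude that the study is underpowered. The reply adds that alpha appears only as an input to the sample size. The analysis section sets no p value cut-off, so a result with p = 0.01 would be reported with a 95% CI that excludes zero, and misreading it is unlikely. Nor does a 95% CI strictly rule out a stricter test level.

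Much of this stands. The slip is almost certainly one of notation, the low power figures show only that the printed inputs are inconsistent, and the 95% CI is evidence for the intended level rather than a formal contradiction of the printed one. It does not follow that the text can stay. Because the analysis section gives no threshold of its own, the printed alpha is the only one available, and the sentence attaches it to rejection of the null hypothesis. A reader has to redo the calculation to learn that it is wrong.

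**Conclusion.** The concern holds. The alpha as printed is wrong: at 0.05%, 64 per group has 23.6% power (two-sided t-test) rather than 80%, and 80% would take 153 per group. At two-sided 5% the plan's figures reproduce, with 64 per group and 80.1% power.

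The finding is an error in the stated significance level, by a factor of 100. It is not evidence that the planned study is too small. The figures assume a two-sample t-test with the stated SD and difference, equal groups, and all 64 per group completing. The two-sided reading is inferred, because it is the only one tried that returns 64 per group at 80% power and because it agrees with the planned 95% CI. Neither one-sided reading changes the conclusion about the printed level.

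**What to change.** In the Sample size calculation section, replace the printed alpha of 0.05% with a two-sided alpha of 0.05 (5%). Keep 64 per group, 128 completers and 150 recruited. Confirm that the full protocol and any analysis plan carry the same level, and make the correction before the primary analysis so that the threshold is settled before results are seen.

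The cost is one phrase of text. No participant, visit, recruitment target, model or interval changes.

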## Abstract

**Introduction:**

COVID-19 may lead to long-term endothelial consequences including hypertension, stroke and myocardial infarction. A pilot study ‘COVID-19 blood pressure endothelium interaction study’, which found that patients with normal blood pressure (BP) at the time of hospital admission with COVID-19 showed an 8.6 mm Hg higher BP ≥12 weeks after recovery, compared with a group without COVID-19. The ‘LOnger-term effects of SARS-CoV-2 INfection on blood Vessels And blood pRessure’(LOCHINVAR) study is designed to provide definitive evidence of the long-term impact of COVID-19 on BP.

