Prior studies on the relationship between COVID-19 and the cardiovascular system are limited by case selection and retrospective data collection. A prospective pilot study ‘COVID-19 BP endothelium interaction study’ (ClinicalTrials.gov NCT04409847, funded by the Chief Scientific Office)^5^ compared 12-week postdischarge ambulatory BP measurements in non-hypertensive patients discharged from hospital after an admission with COVID-19 or a non-COVID diagnosis. This study showed that non-hypertensive COVID-19 patients had an 8.6 mm Hg higher 24-hour systolic BP (SBP) at 12 weeks postdischarge compared with those that did not have COVID-19 infection. A definitive prospective study with longer follow-up is required to confirm if BP is higher in post-COVID-19 patients and whether the higher BP is sustained over a longer period. The LOnger-term effects of SARS-CoV-2 INfection on blood Vessels And blood pRessure (LOCHINVAR) study is designed to answer this question along with pathophysiological studies through deep vascular phenotyping and biomarker studies of endothelial function and vascular injury. The LOCHINVAR study will help generate crucial evidence on the long-term impact of COVID-19 on BP and with information from our mechanistic studies which will facilitate the prioritisation of targetable molecular pathways that can rapidly progress into potential therapies and clinical trials.^6^

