**Figure 1 F1:**
[figure not shown]
Study design, inclusion and exclusion criteria and study procedures. ABPM, ambulatory blood pressure monitoring; AF, atrial fibrillation; BMI, body mass index; BP, blood pressure; eGFR, estimated glomerular filtration rate; IAU, Immediate Admissions Unit. NSAID, non-steroidal anti-inflammatory drugs; OBELIX, COVID-19 blood pressure endothelium interaction study; QEUH, Queen Elizabeth University Hospital Glasgow; SBP, systolic blood pressure.

Control participants will be recruited from hospital admission records or through advertisement. Control patients recruited from hospital admission records will have an admission with COVID-19 like symptoms but are SARS-CoV-2 RT-PCR negative and have chest X-ray or CT (if performed during the relevant admission) that show low probability of COVID-19 and are SARS-CoV-2 IgG antibody negative at enrolment.

Controls recruited through advertising should have had no history of SARS-CoV-2 infection or have had a negative RT-PCR test previously and should have a negative SARS-CoV-2 IgG antibody test at enrolment. Controls will be matched for age, sex and diabetes status with cases by review of demographics of recruited cases and controls at 3 monthly intervals.

OBELIX participants have consented to be recontacted and will be invited to take part in the 12-month and 18-month follow-up visits in the LOCHINVAR study.

Screening for eligibility of all potential participants will be carried out by a member of the study team through review the electronic health record and electronic prescribing records or questionnaire responses. All participants identified as potentially eligible based on the inclusion criteria will be given a participant information sheet for the study containing contact details for the study team and given sufficient time to consider taking part. If the participant is interested, they will contact a member of the study team to discuss further and if they confirm interest in participating in the study, they will provide written, informed consent. Participants may withdraw from the study at any time.

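### Up to 48 of the 150 participants are the pilot patients whose result the study is meant to confirm, so the pooled 12-month estimate is not fully independent of the pilot

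*Protocol article*

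**What the plan says.** The Abstract says that the "study is designed to provide definitive evidence of the long-term impact of COVID-19 on BP". The Introduction gives the result behind it: in the OBELIX pilot, "non-hypertensive COVID-19 patients had an 8.6 mm Hg higher 24-hour systolic BP (SBP) at 12 weeks postdischarge" than patients without COVID-19. It names two aims for the new study: to confirm that pressure is higher after COVID-19, and to learn whether the rise lasts.

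The pilot participants are then brought into the new study. Under participants and recruitment, they "will be invited to take part in the 12-month and 18-month follow-up visits in the LOCHINVAR study". The Sample size section fixes their role in the count: "The study requires a total of 150 subjects to be recruited (128 completed subjects"), then "OBELIX has recruited 48 subjects and these participants will be invited into LOCHINVAR", and "The LOCHINVAR study will recruit the remaining subjects".

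The primary outcome is mean 24-hour systolic pressure at 12 months. The Statistical analysis section specifies one linear regression of it on SARS-CoV-2 status, with covariates that include age, sex and BMI. The article does not distinguish pilot participants from new ones in this analysis.

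**The concern.** A result is confirmed when people who did not produce it show it again. Here some of the confirming sample are the people who produced it. If the pilot cases happened to have higher usual pressure than the pilot controls, the same people will still tend to differ at 12 months. Part of the pooled difference would then be the pilot finding seen a second time, and it would read as a sustained effect of COVID-19.

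At stake is what may be claimed from a positive result. With one pooled estimate, a reader cannot tell replication in new people from carry-over in the old ones.

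**Working it through.** **Inputs from the article.** 48 pilot participants; 150 recruited and 128 completed (64 per group); SD 10 mm Hg; target difference 5 mm Hg; about 15% missing data; pilot difference 8.6 mm Hg at 12 weeks.

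**Assumptions, because the article does not give them.** Within-person correlation r between 12 weeks and 12 months: 0.3 to 0.9. Pilot split: 24/24, with all 48 contributing to the 8.6. All 48 join and are lost at the same rate as others. Tests are two-sided.

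**1. The plan's own figure.** For 5 mm Hg, SD 10, two-sided alpha 0.05 and 80% power, the t-test needs 63.8, so 64 per group, as stated. Power at 64 is 80.1%. (Alpha is printed as 0.05%. Taken literally it would need 150 per group, so 5% is meant. That is a separate matter.) 128/0.85 = 151, against 150 stated.

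**2. Share from the pilot.** 48/150 = 32% of those recruited. 48 × 128/150 = 41 completers, so f = 41/128 = 0.320.

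**3. Bias if the pilot difference was all chance.** The pilot participants' expected 12-month difference is r × 8.6, diluted by f in the pooled estimate:

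- r = 0.3: 0.320 × 0.3 × 8.6 = 0.83 mm Hg
- r = 0.5: 1.38
- r = 0.7: 1.93
- r = 0.9: 2.48

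**4. Type I error given the pilot result.** The null is no COVID-19 effect at either time. The pilot statistic is z = 8.6/(10 × √(2/24)) = 2.98. Given it, the pooled statistic has mean √f × r × 2.98 and SD √(1 − f × r²). The rejection rate is the probability beyond ±1.96.

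| r | mean | SD | rejection rate |
|---|---|---|---|
| 0 | 0 | 1 | 5.0% |
| 0.3 | 0.51 | 0.986 | 7.6% |
| 0.5 | 0.84 | 0.959 | 12.4% |
| 0.7 | 1.18 | 0.918 | 19.8% |
| 0.9 | 1.52 | 0.861 | 30.4% |

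**5. Sensitivity.**

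- The formula gives the 41 completers the full z of the 48. If the 41 are instead a random subset, the mean is bias/SE with SE = 10 × √(2/64) = 1.77, and the SD is √(1 − f × r² × 41/48). At r = 0.3 these are 0.83/1.77 = 0.47 and 0.988, giving 7.2%. At r = 0.9 they are 2.48/1.77 = 1.40 and 0.882, giving 26.4%. This is slightly lower and leads to the same conclusion.
- Conditioning only on a significant positive pilot, rather than on 8.6 exactly: 6.5% to 19.0% over the same r.
- Only 24 of 128 completers from the pilot: 6.5% to 19.3%, given 8.6.
- Not conditioning on the pilot: 5.0%.

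**6. New participants only.** 150 − 48 = 102 recruited; 102 × 0.85 ≈ 87 completers, about 43.5 per group. Power for 5 mm Hg is 63% to 64% by the t-test. SE = 10 × √(2/43.5) = 2.14, so the 95% half-width is 1.96 × 2.14 = 4.2 mm Hg, against 1.96 × 1.77 = 3.5 mm Hg pooled.

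**7. Contrast between cohorts.** With 20.5 and 43.5 per group, SE = √(200/20.5 + 200/43.5) = 3.8 mm Hg, giving about 26% power to detect a 5 mm Hg discrepancy.

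**The case against.** A reader might infer that the primary test's true type I error exceeds 5%. The article does not support that. The primary outcome is a new reading at 12 months, so the pilot data are not tested twice. Dependence arises only through within-person correlation. The excess also requires conditioning on a positive pilot and at least part of the 8.6 mm Hg being chance. The article gives no p value, interval or group split for the pilot, and no correlation. The upper figures take the whole difference as chance, the least favourable case.

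Nor can one say that a third of the sample are pilot participants. They are invited, uptake is unknown, and 32% is a ceiling.

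The study is openly presented as a follow-up of the pilot, and re-examining pilot participants suits the question of whether the rise lasts. It never claims independence from the pilot in so many words. The covariate list is open-ended and the analysis plan is not shown, so the absence of a cohort term or a sensitivity analysis is not in itself a fault.

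The Abstract, unlike the Primary outcome section, describes a change. If the pilot reading were the baseline of a change score, the carry-over would run the other way: 0.320 × (0.7 − 1) × 8.6 = −0.8 mm Hg at r = 0.7.

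Confounding between cases and controls is a different problem. It is not created by reusing pilot participants and can equally affect new recruits.

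All of this limits the size of the problem. What stands is that the article itself fixes the sample's make-up, the power that relies on it and the aim to confirm. Because the study exists to confirm a positive pilot, the error rate given that pilot is a relevant one.

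**Conclusion.** The pooled 12-month result is not fully independent of the pilot it is meant to confirm. Over the assumed correlations of 0.3 to 0.9, with 41 of 128 completers from the pilot, a 24/24 split and all 8.6 mm Hg due to chance, the bias is about 0.8 to 2.5 mm Hg, or 17% to 50% of the 5 mm Hg target. The type I error given the positive pilot is about 8% to 30%. These are scenarios, not properties of the test. Unconditionally it is 5%, and lower uptake or a partly real pilot effect shrinks the excess. The pooled analysis remains usable. What needs limiting is the claim of confirmation made from it.

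**What to change.** Keep the pooled regression as primary. Pre-specify the same model in newly recruited participants only, report it beside the pooled result with its 95% CI as the independent estimate, and state its power (about 63% for 5 mm Hg with about 87 completers). Describe the pooled result as not fully independent of the pilot.

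A cohort term may be added for differences in recruitment source. It removes mean differences between cohorts but not a case-control difference carried over within the pilot cohort, so it cannot replace the new-only model. Give the cohort-by-COVID contrast descriptively only; with an SE of about 3.8 mm Hg it cannot serve as a test of agreement.

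The cost is one extra model and some wording, with no added recruitment or visits. The downside is the wider new-only interval (about ±4.2 against ±3.5 mm Hg). At that power, a non-significant new-only result should not be read as failure to replicate.
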